### Statistical methods

We initially perform a descriptive analysis on age, gender, medication, illness duration etc. The two groups are compared within groups and between groups using F-tests and chi-squared tests. Additionally, we compare the groups on outcome measures at baseline.

Data analysis for the RCT will be performed using mixed effects linear regression with subject specific random effects. The intervention group will be initially compared with the control group on change of all outcome measures after 4 and 8 weeks. Age and gender will be added as covariates in all regression analyses. Repeated-measures analysis of variance (RM-ANOVA) will be used to compare results from baseline follow-up one and follow-up two.

Finally, a descriptive analysis of the playlists is included in the study, i.e. analysis of playlist preferences (style, duration, time of day) in the group of patients benefitting most from treatment compared to the group of patients benefitting the least.

Blinding of the researchers performing the scorings before and after the treatment as well as the subjects of the study will not be possible. Patients will be anonymized when analyzing data. All main analyses will be carried out based on the intention-to-treat principle. Information on adherence is obtained from the Music Star log file data. Compliance rate will be part of the primary study publication.

In case treatment is associated with dropout rate, we will investigate differences in baseline characteristics between complete cases and patients that are lost to follow-up. Any baseline characteristics that are significantly different between these two groups will be used as adjustment parameters in a sensitivity analysis of music listening treatment on the primary outcome.

A multiple comparisons analysis will not be performed, since the results of the analyses of music listening treatment on secondary outcome are purely exploratory, in which case multiple testing analysis is less important [26].

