### Trial design

A single-center randomized controlled trial in a two-arm parallel-group design is conducted from May 2018 to December 2019 following the revised Consolidated Standards of Reporting Trials (CONSORT) guidelines [15]. The RCT includes two groups of participants, an experimental group and a waitlist control group. Both groups receive standard treatment for depression following national guidelines.

The duration of the intervention is 4 weeks. The participants are followed for 8 weeks. Participation takes place in the home of the patient. In addition, three scheduled visits to the hospital in relation to the research project are required. Baseline assessment is performed on the starting day. Follow-up measurements are performed after 4 and 8 weeks (Fig. 3).

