### Sample size

Based on a previous study, we assume that the mean decrease in Pittsburgh Sleep Quality Index (PSQI) scale is 3.04 (SD 2) points for the music intervention group and 2.04 (SD 1.67) points for the waitlist control group after 4 weeks of follow-up [17]. When estimating the sample size, we assume that 25% of the eligible patients will be willing to participate in the project. Based on the patient flow in the outpatient clinic and the available resources from the staff recruiting the patients, we assume that a total of 120 participants can be recruited over a period of 18 months. A dropout rate of 20% is expected. Hence, a total of 100 randomized patients are expected to complete the study. Based on the Satterwaite’s two-sample *t* test and with a total of 100 patients (*n* = 50 per group) the power of our study is estimated to be 76% (at a confidence level of 5%).

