### Outcome measures

#### Primary outcome measure

We assess subjective quality of sleep through patient self-reports using the PSQI to obtain data on psychological and emotional well-being.

The primary endpoint is defined as change of subjective sleep quality from baseline at 4 weeks. Treatment benefit is achieved when the PSQI score is decreased with statistical significant change after the 4-week intervention period.

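### In its default form, the planned mixed model lets week-8 scatter help set the standard error of the primary week-4 contrast; visit-specific variances would avoid this at almost no cost

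*Protocol article*

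**What the plan says.** Under Statistical methods, the article names the model family: "Data analysis for the RCT will be performed using mixed effects linear regression with subject specific random effects". It then gives the comparison: "The intervention group will be initially compared with the control group on change of all outcome measures after 4 and 8 weeks". Adjustment is stated too: "Age and gender will be added as covariates in all regression analyses". A repeated-measures ANOVA over baseline and both follow-ups is also planned.

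Under Primary outcome measure: "The primary endpoint is defined as change of subjective sleep quality from baseline at 4 weeks". Under Trial design: "The duration of the intervention is 4 weeks. The participants are followed for 8 weeks". The week-8 assessment therefore falls four weeks after the music period has ended.

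The Sample size section plans on week-4 variability only. Its assumption for the music arm is that "the mean decrease in Pittsburgh Sleep Quality Index (PSQI) scale is 3.04 (SD 2) points for the music intervention group". For the control arm, it puts the same decrease at 2.04 with an SD of 1.67. From these figures it derives 76% power for a Satterthwaite two-sample t test with 50 patients per group.

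The article does not say whether the random effect is an intercept only or whether residual variance may differ by visit. It also leaves open whether the response is the two change scores or the three raw scores, and whether standard errors are model-based or robust.

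**The concern.** The primary question concerns one visit, but the named model handles the visits together. Taken in its most common default form, a random-intercept model with one residual variance gives the two change scores the same variance. The standard error of the week-4 arm contrast is then built from an average of the two visits' variances.

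Nothing in the article supports equal scatter at the two visits. Week 4 closes the intervention period. Week 8 is twice as far from baseline and follows a month without the intervention. If week-8 change is more variable, the primary test becomes conservative and loses power, from a planned level of only 76%. If it is less variable, the primary test exceeds its nominal 5%. In either case the analysis no longer matches the power calculation, which uses the week-4 SDs alone.

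**Working it through.** **Inputs from the article.** Difference in mean 4-week change 3.04 − 2.04 = 1.00; SDs 2 and 1.67; 50 per group; 5% level, taken as two-sided.

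**Assumed input.** r = SD of 8-week change divided by SD of 4-week change. The article gives no week-8 SD, so r is varied. Age and gender adjustment is ignored.

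**Step 1: the article's own figure.** SE = √(2²/50 + 1.67²/50) = √(6.7889/50) = 0.368, with Satterthwaite df 95.0. The noncentral t gives power of 76.6%, which reproduces the stated 76%. A normal approximation with the root-mean-square SD, √(6.7889/2) = 1.842, gives 77.5%. That value is the baseline for the table below.

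**Step 2: joint random-intercept model of the two change scores.** With arm, visit, arm-by-visit and one residual variance, the model variance at each visit is (Var4 + Var8)/2. Hence

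model SE / true week-4 SE = k = √((1 + r²)/2).

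The actual type I error is 2[1 − Φ(1.96k)]. Power is Φ(1/0.368 − 1.96k), the other tail being negligible.

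| r (assumed) | k | model SE | type I error, week 4 | power, week 4 |
|---|---|---|---|---|
| 0.8 | 0.906 | 0.334 | 7.6% | 82.6% |
| 0.9 | 0.951 | 0.351 | 6.2% | 80.2% |
| 1.0 | 1.000 | 0.368 | 5.0% | 77.5% |
| 1.1 | 1.051 | 0.387 | 3.9% | 74.3% |
| 1.25 | 1.132 | 0.417 | 2.7% | 69.0% |

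The higher power for r below 1 is not a gain, because the test is then oversized. With a separate variance for each visit, the SE stays at 0.368 and power at 77.5% for every r.

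**Step 3: check by fitting the model.** REML random-intercept fits to simulated data (200 runs per ratio, within-patient correlation assumed 0.6) gave a mean model SE of 0.330 at r = 0.8, 0.368 at r = 1 and 0.416 at r = 1.25. The true value is 0.368. This agrees with the formula; 200 runs are too few to estimate rejection rates well.

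**Step 4: other models that fit the wording.**
- *Random intercept on the three raw scores.* The model variance of 4-week change is the mean of the three pairwise difference variances, so week-8 data still enter. With SD 3 at each visit and correlations 0.7 (0–4), 0.5 (0–8) and 0.7 (4–8), these variances are 5.4, 9.0 and 5.4. Their mean is 6.6 and the SE ratio is √(6.6/5.4) = 1.11. With correlations 0.7, 0.6 and 0.8 they are 5.4, 7.2 and 3.6. Their mean is 5.4 and the SE ratio is exactly 1.00, although the two change variances differ. All of these SDs and correlations are assumed.
- *Random intercept and slope on the raw scores.* With slope variance s² per week² and residual variance e², Var(change4) = 16s² + 2e² and Var(change8) = 64s² + 2e². For s² = 0.05 and e² = 1.5 these are 3.8 and 6.2. Equality is not forced, but week-8 change cannot be the less variable of the two.
- *Visit-specific residual variances, or robust standard errors.* Either removes the problem.

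**The case against.** A reader might infer that the quoted wording can only mean a random intercept with equal variances, and that the week-4 standard error is therefore wrong whenever the two visits differ in scatter. The article does not support that. A subject random intercept with a separate residual variance at each visit has three parameters for the three covariance terms of two change scores. It is identifiable, and it is still a mixed model with a subject-specific random effect. Comparing arms on change can also be done from raw scores through arm-by-visit terms, where a random slope can be fitted. The raw-score example with an SE ratio of 1.00 shows that unequal change variances do not always distort the week-4 result.

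Residual covariance and type of standard error are details that a condensed article commonly leaves to the analysis plan, which is not shown. Their absence is not a fault. No figure in the article shows that the two SDs differ. The natural argument, a longer interval after the intervention has stopped, points to more scatter at week 8. That costs power on the primary test and does not inflate its type I error. The matching inflation would fall on the week-8 tests (by the same formula, k = √((1 + 1/1.25²)/2) = 0.906, or 7.6%, at r = 1.25), and the article treats the secondary outcomes as exploratory.

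All of this stands, and it limits the point to a recommendation. It does not remove the point. The article does name a random-effects structure, the default form of that structure pools variance across visits, and the power calculation does not.

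**Conclusion.** The point holds as an improvement to the stated model, not as a demonstrated error. It applies fully to a joint change-score model with a random intercept, one residual variance and model-based standard errors. For assumed SD ratios of 0.8 to 1.25, the primary type I error there runs from about 7.6% to 2.7%, and at 1.25 power falls by 77.5 − 69.0 = 8.5 percentage points. Within 0.9 to 1.1 the standard error is off by about 5% and the type I error lies between 6.2% and 3.9%, which is minor. A random-intercept model of the raw scores also draws on week-8 data, by an amount that depends on the correlations. The stated 76% power is correct for the week-4 t test and is not in question. The real SD ratio cannot be known from the article.

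**What to change.** In Statistical methods, replace the subject random effect with an unstructured covariance across visits, for each outcome. Fixed effects: arm, visit, arm-by-visit, age and gender. Fit by REML with Satterthwaite or Kenward-Roger degrees of freedom. State that the primary result is the arm contrast in PSQI change at week 4, taken from this model.

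This takes a sentence or two of text. Compared with a random intercept plus residual (two covariance parameters), it adds one parameter if the two change scores are modelled (three in all), or four if all three raw visits are modelled (six in all). About 100 patients support that easily. If the variances turn out equal, next to nothing is lost. If they differ, the week-4 standard error reflects week-4 variability, as the sample size calculation assumed.

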### Randomization

Randomization takes place when the inclusion document has confirmed eligibility and the informed consent has been signed following the regulations of the The North Denmark Region Committee on Health Research Ethics Randomization is carried out by the use of REDCap (Research Electronic Data Capture) hosted at Aalborg University Hospital. REDCap is a secure web-based application designed to support data capture for research studies. The randomization will be stratified according to age, i.e., under 30 years versus 30 years and above. Randomization is performed using computer-generated block randomization (random block sizes 2–8) with 1:1 allocation between the intervention group and the waitlist control group.

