#### Secondary outcome measures

We assess sleep quality using actigraphy to obtain objective sleep data. We assess symptoms of depression using HAM-D17 to obtain data on the depressive state. Finally, we assess quality of life using WHO-5 and WHOQOL-BREF to obtain data on psychological well-being considering mood, vitality, and interests (WHO-5) and physical/psychological health, social engagement, and environment (WHOQOL-BREF).

The secondary outcome measures are selected to address these objectives (secondary outcome measure 2, 4, 6, and 8). Measuring change from baseline at 8 weeks, assess sustainability of results, and progression of symptoms over time (secondary outcome measure 1,3,5,7, and 9).

The nine secondary endpoints are defined and listed below:
Subjective sleep quality (PSQI): Change of sleep quality from baseline at 8 weeksObjective sleep quality (Actigraphy): Change of sleep quality from baseline at 4 weeksObjective sleep quality (Actigraphy): Change of sleep quality from baseline at 8 weeksSymptoms of depression (HAM-D17): Change of depression level from baseline at 4 weeksSymptoms of depression (HAM-D17): Change of depression level from baseline at 8 weeksQuality of life (WHO-5): Change of quality of life from baseline at 4 weeksQuality of life (WHO-5): Change of quality of life from baseline at 8 weeksQuality of life (WHOQOL-BREF): Change of quality of life from baseline at 4 weeksQuality of life (WHOQOL-BREF): Change of quality of life from baseline at 8 weeks

All outcome measures are collected at baseline, after 4 weeks experimental/wait-list control and again after 4 weeks of follow-up. In addition, registration of pharmacological treatment during the period of participation is included in the data collection.

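### The arms are compared on PSQI change without baseline PSQI as a covariate, which gives up precision in a trial planned at 76% power, and an RM-ANOVA is listed beside the mixed model with no stated role

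*Protocol article*

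**What the plan says.** Under *Primary outcome measure* the protocol article states: "The primary endpoint is defined as change of subjective sleep quality from baseline at 4 weeks". Under *Secondary outcome measures* it states: "All outcome measures are collected at baseline, after 4 weeks experimental/wait-list control and again after 4 weeks of follow-up". A baseline PSQI is therefore planned for every participant.

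*Statistical methods* sets out the analysis in this order:

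- a descriptive comparison of the arms, which includes the outcomes: "Additionally, we compare the groups on outcome measures at baseline";
- the model: "Data analysis for the RCT will be performed using mixed effects linear regression with subject specific random effects";
- the quantity compared: "The intervention group will be initially compared with the control group on change of all outcome measures after 4 and 8 weeks";
- the covariates: "Age and gender will be added as covariates in all regression analyses";
- a second method: "Repeated-measures analysis of variance (RM-ANOVA) will be used to compare results from baseline follow-up one and follow-up two".

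Baseline PSQI thus enters in two certain ways, through subtraction in the change score and through the descriptive baseline comparison. A third way is conditional. If dropout is related to treatment, baseline characteristics that differ between completers and those lost become adjustment terms in a sensitivity analysis. Baseline PSQI is not named as a covariate in the main model.

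**The concern.** Subtracting the baseline is not the same as adjusting for it. A change score fixes the slope of week-4 PSQI on baseline PSQI at 1. When the true slope is below 1, part of the baseline variation stays in the outcome as noise, and a chance difference between the arms at baseline carries into the estimated effect. Comparing the arms at baseline reveals such a difference but does nothing about it.

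The article plans for only 76% power, so precision that is available from data already being collected matters. Benefit is also defined by statistical significance of the PSQI change, so it should be clear which test decides. The article names a mixed model and then an RM-ANOVA on the same three visits, and it does not say what the second is meant to answer.

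**Working it through.** **Inputs from the protocol article (*Sample size*).** Mean PSQI decrease 3.04 (SD 2) with music and 2.04 (SD 1.67) on the waitlist; Satterthwaite two-sample t test; 50 per arm; 5% level; stated power 76%. Recruitment is 120 with 20% dropout, and 120 × 0.8 = 96, or 48 per arm.

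**Input not in the document.** The correlation rho between baseline and week-4 PSQI. It is assumed and varied below.

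**Step 1: reproduce the stated power.** Difference = 3.04 − 2.04 = 1.00. SE = √[(2² + 1.67²)/50] = √(6.789/50) = 0.368. Noncentrality = 1.00/0.368 = 2.71 on about 95 df. Two-sided power at 5% is 76.6%, which agrees with the stated 76%; the one-sided figure, 85.3%, does not. At 48 per arm, power is 74.9%. The plan's figure is therefore the power of an unadjusted comparison of change.

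**Step 2: effect of adjusting for baseline.** Let the SD be σ at both visits.

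- Variance of a change score: 2σ²(1 − rho).
- Residual variance after adjustment for baseline: σ²(1 − rho²).
- Ratio: (1 − rho²)/[2(1 − rho)] = (1 + rho)/2.

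The ratio is below 1 for every rho below 1. If the variances differ and k is baseline SD over week-4 SD, the ratio is (1 − rho²)/(1 + k² − 2·rho·k). The denominator exceeds the numerator by (k − rho)², so, apart from the degree of freedom spent, adjustment is never less precise.

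**Step 3: power with baseline PSQI in the model.** Both change SDs are multiplied by √[(1 + rho)/2].

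| rho (assumed) | Variance ratio | Power, 50 per arm | Power, 48 per arm |
|---|---|---|---|
| not adjusted | 1 | 76.6% | 74.9% |
| 0.5 | 0.75 | 87.3% | 85.9% |
| 0.7 | 0.85 | 83.0% | 81.4% |
| 0.8 | 0.90 | 80.8% | 79.2% |
| 0.9 | 0.95 | 78.7% | 77.0% |

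**Step 4: which rho fits the article's own SDs.** The average variance of change is (4 + 2.789)/2 = 3.394. Setting this equal to 2σ²(1 − rho) gives rho = 1 − 3.394/(2σ²). The PSQI runs from 0 to 21, and the article gives no SD for the score itself, so σ is assumed.

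| PSQI SD (assumed) | Implied rho | Power, 50 per arm | Gain over 76.6% |
|---|---|---|---|
| 2.5 | 0.73 | 82.4% | 5.8 points |
| 3 | 0.81 | 80.6% | 4.0 points |
| 3.5 | 0.86 | 79.5% | 2.9 points |
| 4 | 0.89 | 78.8% | 2.2 points |

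In the other direction, rho 0.5 needs a PSQI SD of √[3.394/(2 × 0.5)] = 1.84, and rho 0.7 needs √[3.394/(2 × 0.3)] = 2.38. The larger gains in Step 3 thus require a narrow spread of scores.

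**Step 5: the RM-ANOVA.** With two arms and three visits, its group-by-time test has 2 degrees of freedom and asks whether the arms differ in their pattern over baseline, week 4 and week 8. The primary endpoint concerns one contrast, between arms at week 4. A simulation (4,000 runs per setting, 50 per arm, complete data, equal correlations of 0.3, 0.5 or 0.7, a 1-point effect at week 4) compared this test with the week-4 change test. They gave different significance verdicts in about 12 to 13% of trials. Power of the group-by-time test was about 66 to 67% if half the effect remained at week 8, and about 79 to 81% if all or none remained. It is a different test, not a uniformly weaker one.

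**The case against.** **The article is condensed.** It says that age and gender will be added, not that nothing else will be, and a full covariate list may sit in an analysis plan that is not shown. A mixed model that takes baseline as an outcome with a common mean in both arms would be about as efficient as adjustment. This carries weight, but the article is not silent. It fixes the quantity compared (change) and names the covariates for all regressions. The form of the age term, given stratification at 30 years, is routine detail and no part of this point.

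**Bias.** A reader might infer that omitting baseline PSQI biases the result. It does not. Allocation is randomised 1:1, and the change-score contrast is unbiased over randomisation. The cost is precision, and sensitivity to whatever imbalance happens to arise.

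**Complete cases and intention to treat.** A reader might infer that the RM-ANOVA is a complete-case analysis that breaks the intention-to-treat commitment. The article does not say so. It mentions complete cases only when it compares completers with those lost to follow-up, and it pledges intention to treat for the main analyses without saying that the RM-ANOVA is one. Classical RM-ANOVA software does drop people with a missing visit, but that is an inference about how it would be run. The timing of dropout is not given, so any extra loss against a 4-week analysis could be anywhere from none to all of the 24 expected dropouts (20% of 120).

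**Power and role of the RM-ANOVA.** It takes no power from the mixed model. It can fairly be read as a supportive look at the course over time, since the article gives the 8-week measures the separate purpose of showing sustainability and progression. On that reading nothing is contradicted; only the label is missing.

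**Size of the gain.** Quoting only rho 0.5 to 0.7 would be selective, as Step 4 shows.

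**Conclusion.** The point holds as a matter of efficiency and clarity. As written, the main comparison uses change scores with age and gender as the only named covariates, and it leaves unused a baseline value that is already collected. At 50 per arm, adjustment raises power from 76.6% to about 87% at rho 0.5, 83% at 0.7, 81% at 0.8 and 79% at 0.9. The article's own SD of change points to the upper part of that range unless the PSQI SD is below about 2.4. With an SD between 2.5 and 4, the gain is about 2 to 6 percentage points.

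These figures rest on equal variances at baseline and week 4 and on an assumed rho or PSQI SD, none of which the document gives. That adjustment does not worsen precision, apart from the degree of freedom spent, needs none of these assumptions.

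Separately, the RM-ANOVA has no stated role, and its group-by-time test is not the primary contrast. This is a gap in labelling. The text supports neither a claim of bias nor a claim that intention to treat is breached.

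**What to change.** In *Statistical methods*:

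1. Add the baseline value of each outcome, with its interaction with visit, to the mixed model alongside age and gender. Alternatively, specify a mixed model with baseline among the outcomes and a common baseline mean in both arms.
2. Name the 4-week between-arm contrast for PSQI from that model as the primary result. The 8-week contrast stays secondary.
3. Delete the RM-ANOVA, or label it supportive and say what it is meant to show.

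The cost is one or two degrees of freedom and a few sentences of text. No new data, visits or participants are needed.

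### The one missing-data sensitivity analysis described runs only if dropout differs by arm and picks its covariates by significance, so it can stay silent or miss real predictors

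*Protocol article*

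**What the plan says.** All of this is in the protocol article, mostly under Statistical methods.

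- **Main analysis:** "Data analysis for the RCT will be performed using mixed effects linear regression with subject specific random effects". Also, "Age and gender will be added as covariates in all regression analyses", and "All main analyses will be carried out based on the intention-to-treat principle".
- **Gate on the sensitivity analysis:** "In case treatment is associated with dropout rate, we will investigate differences in baseline characteristics". The comparison is "between complete cases and patients that are lost to follow-up". How association is to be judged is not stated.
- **Covariate rule:** "Any baseline characteristics that are significantly different between these two groups will be used as adjustment parameters in a sensitivity analysis". It applies to the primary outcome only, which is PSQI change from baseline at 4 weeks (Primary outcome measure).
- **Expected loss (Sample size):** "A dropout rate of 20% is expected", with the assumption that "a total of 120 participants can be recruited over a period of 18 months".

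No other sensitivity analysis for missing data is described.

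**The concern.** The rule has two stated parts, and each uses the wrong criterion.

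**The gate.** Bias from dropout depends on who leaves and why, not only on how many leave each arm. Two arms can each lose 20% and still be left with completers who are not comparable. Several features make arm-specific reasons plausible here. Neither patients nor raters are blinded, and the primary outcome is self-reported. The music arm has a nightly task for four weeks. The waitlist arm is offered the equipment after week 8, partly to keep controls in the trial (Trial design), so the incentives to stay differ by arm. When the rates look similar, the check is skipped.

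**The screen.** A baseline variable is useful for adjustment if it predicts PSQI. Whether it differs significantly between a small group of dropouts and the completers is a different question, and the sample answers it with low power.

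A further limit applies even when the check runs. Adjusting for baseline variables cannot show what happens if dropout depends on the week-4 PSQI that was never observed. Readers could then be told that dropout was examined when the question that matters was not.

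**Working it through.** **Inputs.** From Sample size: 120 recruited, 20% dropout, PSQI decrease 3.04 (SD 2) with music and 2.04 (SD 1.67) on waitlist. From Randomization: 1:1 allocation, so 60 per arm. Assumed: association and significance judged at two-sided 0.05, and the dropout mechanisms in step 4.

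**1. The plan's own figure.** With 50 per arm, SE = √(2²/50 + 1.67²/50) = √(0.0800 + 0.0558) = 0.368. The noncentrality is 1.00/0.368 = 2.71, on about 95 Satterthwaite degrees of freedom. Two-sided power is 76.6%, so the stated 76% reproduces. Expected loss is 0.20 × 120 = 24, leaving 96.

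**2. How often the gate opens.** Exact binomial probabilities, 60 per arm:

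| True dropout | Chi-square p < 0.05 | Fisher p < 0.05 |
|---|---|---|
| 20% and 20% | 5% | about 3% |
| 15% and 25% | 28% | 20% |
| 10% and 30% | 80% | not needed here |

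With 24 dropouts, z = (a − b)/60 ÷ √(0.2 × 0.8 × 2/60), and the denominator is 0.0730. A 16:8 split gives 0.1333/0.0730 = 1.83, p = 0.07, so the gate stays shut. A 17:7 split gives 0.1667/0.0730 = 2.28, p = 0.02, so it opens.

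**3. Power of the covariate screen.** For a standardised baseline difference d, the noncentrality is d/√(1/96 + 1/24) = d/0.228, tested on 118 degrees of freedom.

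| d (SD) | Noncentrality | Power |
|---|---|---|
| 0.3 | 1.31 | 26% |
| 0.4 | 1.75 | 41% |
| 0.5 | 2.19 | 58% |
| 0.645 | 2.83 | 80% |

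The article also expects 100 completers, which would mean 20 lost. The noncentrality at d = 0.4 is then 0.4/√(1/100 + 1/20) = 1.63, so the screen is weaker still.

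**4. What can go unseen.** Simulation with 60 per arm, 20% dropout in both arms, no true effect, and a Welch t test in completers. The slope is the assumed log-odds of dropout per PSQI point of poorer change.

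| Slope, music / waitlist | SDs used | Spurious benefit (points) | Type I error |
|---|---|---|---|
| 0.5 / 0 | 2 and 1.67 | about 0.35 | 15% |
| 0.3 / 0 | 2 and 1.67 | 0.23 | 9% |
| 0.1 / 0 | 1.84 in both | 0.08 | 4.9% |
| 0.5 / 0.25 | 1.84 in both | 0.14 | 7.6% |
| 0.5 / 0.5 | 2 and 1.67 | 0.10 | 5.4% |
| 0.5 / 0.5 | 1.84 in both | about 0 | 4.8% |

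The common SD is √((2² + 1.67²)/2) = 1.84. In the first two settings a Fisher gate opened in about 3% of trials. The sign is not fixed: if good improvers leave the music arm instead (log-odds of 1 per SD of change), the estimate shifts by about 0.35 points against music.

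**5. With a mixed model.** A random-intercept model on baseline, week 4 and week 8 was also simulated, with dropouts contributing baseline only. It assumed baseline SD 3, change SD 1.84 and baseline–change correlation −0.4, omitted age and gender, and used 600 trials per setting. Music-arm slopes of 0.3 and 0.5 gave spurious benefits of 0.17 and 0.23 points and type I errors of 8.7% and 9.8%, against 5.0% with no selection. The Monte Carlo error at 9.8% is √(0.098 × 0.902/600) = 1.2 percentage points. The model reduces the bias but does not remove it.

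**The case against.** **The main analysis is itself a safeguard.** An intention-to-treat mixed model, fitted by likelihood in the usual way, uses all available PSQI values and is valid when missingness depends on observed data in the model. This stands, and it would be wrong to say the plan has no other protection. It does not reach the case at issue: a patient lost before week 4 supplies no post-baseline PSQI, so loss tied to the unseen outcome is not corrected.

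**The absence of a delta or reference-based analysis is an omission that an analysis plan may fill.** This also stands. The article condenses a fuller document, and a missing analysis is not the fault here. The fault is a gate and a selection rule that the article states.

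**The consequences rest on assumed mechanisms.** This is correct. A reader might infer that dropout will commonly bias the primary result, or that the check would usually not run. The documents support neither, because they give no dropout by arm and no reasons for leaving. Nor do they say that association means a test at 0.05. What holds on any reading is that the check is skipped when the rates look similar. Larger biases can be produced, for example 0.63 points if the music arm loses poor improvers and the waitlist arm good ones (log-odds of 1 per SD of change), but nothing in the article points to opposite selection of that strength.

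**Only a sensitivity analysis is affected.** This is true. The primary estimate and test are unchanged, which limits the weight of the point.

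**Conclusion.** The concern holds in a limited form. The gate and the significance screen are both stated, and both perform poorly at this trial's size. The power of the screen follows from the article's own numbers and a 0.05 level; how often the gate opens also depends on the assumed test and true dropout rates.

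The possible bias is conditional. In the settings with selection in the music arm alone, or in the same direction in both arms, it runs from near zero to about 0.35 points among completers (type I error 5–15%) and is about 0.2 points in a mixed model. That is up to roughly a third, or about a fifth, of the planned 1.00-point effect. These figures show what the planned check could fail to reveal; they do not forecast this trial's bias. The point should be addressed, but it does not undermine the primary analysis.

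**What to change.** Change the missing-data paragraph in Statistical methods as follows:

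1. Run the sensitivity analysis of the primary outcome whatever the dropout rates in the two arms.
2. Name its adjustment covariates in advance for their prognostic value for PSQI, for example baseline PSQI and HAM-D17 with age and gender. Drop the selection by p-value. If baseline PSQI is already a response in the mixed model, that part is met.
3. Include a delta or reference-based analysis in which missing music-arm PSQI values are made less favourable. With a delta analysis, report the delta at which the conclusion changes.

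The comparison of completers with patients lost to follow-up can stay as description. The main model's covariates need not change, since the fault lies in the sensitivity analysis.

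The cost is a little more analysis work on data already being collected, and a sensitivity estimate that may be less favourable than the main one.
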